#### Sociodemographic information

2.10.10

Variables will include date of birth, age, biological sex, and date of onset of diabetes. Participant identifiers such as nickname or contact email will be recorded exclusively for study management and access to the intervention platform and will not be used as analytical variables.

Socioeconomic status will be estimated using the Family Affluence Scale III (FAS-III) (53). The FAS-III comprises six items assessing: car ownership, 0–2 points; individual bedroom, 0–1 point; number of computers/tablets, 0–3 points; number of bathrooms, 0–3 points; dishwasher ownership, 0–1 point; and family vacations abroad, 0–3 points. The total FAS-III score is obtained by summing all item scores, ranging from 0 to 13 points, with higher values indicating greater family affluence. Participants will be categorized as having low (0–2 points), medium (3–5 points), or high (≥6 points) status.

#### Psychological assessments

2.10.11

Subjective well-being will be assessed using the *Cuestionario Único de Bienestar Escolar* (CUBE), a validated questionnaire designed to evaluate cognitive and affective components of well-being in children and adolescents (54). The instrument comprises three domains: life satisfaction, positive emotions, and negative emotions. Life satisfaction is assessed through five items scored on a 10-point Likert scale ranging from 0 (“totally disagree”) to 10 (“totally agree”). The emotional items are described as using a 5-point Likert scale ranging from 0 to 5, which comprises six response values.

Negative emotion scores will be reverse-coded so that higher values consistently indicate greater well-being. Because life satisfaction and emotional domains are measured using different response scales, all domain scores will be rescaled to improve interpretability. Domain-specific scores and an overall subjective well-being score will then be calculated, with higher scores indicating better subjective well-being. This questionnaire has previously been used in the Diactive-1 cohort to assess subjective well-being in children and adolescents (55).

#### Generic health-related quality of life

2.10.12

Generic health-related quality of life will be assessed using the KIDSCREEN-10, a validated 10-item unidimensional questionnaire for children and adolescents aged 8–18 years (56). Both the youth self-report and parent-proxy versions will be administered. The KIDSCREEN-10 assesses global perceived health-related quality of life over the previous week, covering physical well-being, energy, mood, loneliness, autonomy and leisure time, family relationships, peer relationships, school functioning, and attention at school. Items are rated on a 5-point Likert scale, ranging from “never” to “always” or from “not at all” to “extremely,” depending on the item. After reverse-coding negatively worded items so that higher scores indicate better health-related quality of life, the KIDSCREEN-10 items will be summed to obtain a raw score, which will be converted into the corresponding Rasch-person parameter and transformed into a norm-based T-score according to the official scoring procedure.

#### Diabetes-specific health-related quality of life

2.10.13

Diabetes-specific health-related quality of life will be assessed using the Spanish version of the DISABKIDS diabetes-specific module (57). Both the youth self-report and parent-proxy versions will be administered to capture the participant’s own and the parent’s or guardian’s proxy perception. The module comprises 10 diabetes-specific items organized into two dimensions reflecting the impact of the disease and the impact of treatment on health-related quality of life. Items are answered on a 5-point Likert scale ranging from 1 (“never”) to 5 (“always”). As all items indicate diabetes-related burden, responses will be reverse-transformed to a 0–100 scale so that higher scores indicate better diabetes-specific health-related quality of life. If an overall diabetes-specific health-related quality of life score is required, it will be derived by combining both dimensional scores as an item-weighted mean according to the number of items contributing to each dimension.

#### Adherence to Mediterranean diet

2.10.14

To evaluate adherence to the Mediterranean diet, the Mediterranean Diet Quality Index for Children and Teenagers (KIDMED) index will be applied (58). This test was previously validated (58), and widely used in the Spanish young population with diabetes (59). The KIDMED index ranges from 0 to 12 and is based on a 16-question test. Items reporting unhealthy characteristics are scored with −1 point, and those reporting healthy characteristics with +1 point. The sum of scores will be used to categorize into 3 levels: (a) optimal Mediterranean diet (>8 points), (b) improvement needed (4 to 7 points), (c) low diet quality (≤3 points).

#### Screening for eating disorders

2.10.15

The risk of having eating disorders will be assessed by the Sick, Control, One, Fat, Food (SCOFF) questionnaire, a five-question test that can be self-administered with an acceptable sensitivity and specificity (60). The Spanish SCOFF questionnaire version has been validated for its use in primary care settings (60). A score ≥2 will indicate risk of eating disorders.

#### App usability

2.10.16

*Expert evaluation:* The Spanish adaptation of the Mobile Application Rating Scale (MARS) will be used for standardized expert assessment of mHealth app quality (61). The MARS includes 23 items rated on a 5-point Likert scale from 1 (“inadequate”) to 5 (“excellent”), organized into four objective quality domains (engagement, functionality, aesthetics, and information quality) and one subjective quality domain. Each domain score will be calculated as the mean of its corresponding items. The overall app quality score will be computed as the mean of the four objective domain scores, while the subjective quality score will be reported separately.

*User evaluation:* User-perceived app quality and usability will be assessed using the Spanish version of the User Version of the Mobile Application Rating Scale (uMARS). The uMARS comprises 20 items rated on a 5-point Likert scale from 1 (“inadequate”) to 5 (“excellent”) and is organized into four domains (engagement, functionality, aesthetics, and information quality). Domain scores will be calculated as the mean of their corresponding items, and the overall app quality score will be computed as the mean of the four domain scores. To complement the uMARS assessment, three open-ended questions will be included to explore users’ perceptions of the app, specifically the most valued features, difficulties encountered during use, and suggestions for improvement. These qualitative responses will provide contextual information.

#### Data recorded by the Diactive-1 app

2.10.17

Intervention delivery and participation data will be captured through the Diactive-1 app throughout the study period. For each completed session, recorded variables will include the session number, date and time of completion, time since training onset, training type, specific exercises performed, number of exercises, sets and repetitions, activity times, and recovery times. The app will also record diabetes management variables, including pre- and post-session glucose values, pre- and post-session glucose trend arrows, hypoglycemic events reported since the previous session, heart rate metrics when available, and subjective perception of exertion after the session. User-reported session satisfaction will also be collected.

### Participant timeline

2.11

Each participant will follow a standardized timeline comprising screening and enrolment, baseline assessment, randomization, a 12-week intervention or usual-care period, post-intervention assessment, and post-T1 data collection. Screening and informed consent or assent may be initiated before the baseline visit.

Baseline procedures will be completed in the following sequence: (i) a baseline clinical visit, during which eligibility will be confirmed, informed consent or written assent will be verified, and sociodemographic, diabetes-related clinical, anthropometric, pubertal-maturation, and handgrip-strength data will be collected; (ii) central randomization immediately after the baseline clinical data have been entered into the Diactive-1 web platform; (iii) completion of the online web-based questionnaires within 48 hours after the baseline visit; (iv) a 7-day baseline data-collection period, during which participants will undergo fasting blood and urine testing and upload all available glucose-monitoring, insulin, and carbohydrate-intake data from their CGM system or insulin pump; (v) upload of the laboratory results and CGM or insulin-pump reports by the clinical research team within the following 72 hours, including glucose-monitoring data covering the 14 days before and 7 days after the baseline clinical visit; and (vi) verification of the completeness of all baseline information, followed by activation of the Diactive-1 app for participants allocated to the intervention group. Thus, intervention exposure will begin only after all baseline assessments and data-collection procedures have been completed and verified. The 12-week intervention or usual-care follow-up period will begin on the date of app activation or the corresponding date for participants allocated to usual care. To facilitate scheduling of the final clinical assessment, the web platform will generate automated alerts 15 and 7 days before the expected Week 12 assessment.

At Week 12, measured from the beginning of the intervention or usual-care follow-up period, the post-intervention procedures will replicate the baseline assessment protocol. Once these data have been uploaded, checked, and verified as complete, participants in the Diactive-1 group will be considered to have completed the intervention but will retain access to the app for continued voluntary use, whereas participants in the usual-care control group will be granted access to the Diactive-1 mHealth app. **Figure 4** provides an overview of the project timeline, and **Table 2** presents the schedule of enrolment, interventions, and assessments.

**Figure 4 f4:**
[figure not shown]
Overview of the Diactive-1 study timeline, including baseline procedures, randomization, intervention and usual-care periods, and post-intervention assessments.

**Table 2 T2:** Schedule depicting the enrollment and interventions for the Diactive-1 Study in accordance with the SPIRIT 2025 guidelines.

Randomization	TRIAL PERIOD			
	Enrollment		Pre-randomization	Post-randomization
Timepoint	*-t_i_* to 0	0	*Baseline t_0_*	*t_1 (12 weeks)_*
ENROLLMENT:				
Eligibility screen	X	X*		
Informed consent	X	X*		
Randomization		X		
INTERVENTION/COMPARATOR:				
Diactive-1 ^a^			↔	↔
Usual care ^b^			↔	↔
ASSESSMENTS:				
Handgrip strength			X	X
Glycemic stability			X	X
Insulin requirements			X	X
Cardiovascular biomarkers and lipid profile			X	X
Anthropometric parameters			X	X
Maturity status			X	X
Self-reported fitness			X	X
Physical literacy			X	X
24-Hour Movement Patterns			X	X
Barriers to physical activity			X	X
Sociodemographic information			X	
Psychological assessments			X	X
Quality of life for youth			X	X
Quality of life for families			X	X
Mediterranean diet			X	X
Eating disorders			X	X
App usability (users/experts)^c^				X
Diactive-1 app parameters^d^			↔	↔

Note: X indicates an assessment or procedure performed at the corresponding timepoint; ↔ indicates continuous delivery, usual-care exposure, or app-based data recording throughout the 12-week study period. Baseline clinical assessments will be completed before randomization, whereas the remaining baseline questionnaires and 7-day diabetes-related data collection will be completed after randomization but before intervention activation.

*Eligibility and consent may be screened before enrolment and confirmed at the baseline visit before randomization.

^a^
Diactive-1 will be activated only after all baseline procedures and data have been completed and verified and will then be delivered for 12 weeks.

^b^
Participants allocated to the usual-care/waiting-list control group will receive usual clinical care during the 12-week study period and will be offered Diactive-1 access after post-T1 7-day data collection.

^c^
App usability will be assessed at the end of the intervention period among participants with access to the app; expert MARS assessment will be reported separately if not linked to participant follow-up.

^d^
Diactive-1 app parameters will be recorded continuously during app use and summarized at the end of the intervention period.

### Adverse event reporting and harms

2.12

At all participating hospitals, usual care includes routine pediatric diabetes follow-up, review of glucose and insulin data, diabetes self-management counseling, and treatment adjustment when clinically indicated. Routine care will not be standardized across sites. Each hospital will provide a brief description of its exercise counseling, follow-up practices, and routine use of CGM, insulin pumps, and automated insulin-delivery systems. Unscheduled clinical contacts and any clinically relevant changes in treatment or diabetes technology during follow-up will be recorded. Adverse events and other health problems will be documented separately from these treatment-related changes.

Moreover, adverse events will be actively monitored at the scheduled study visits and throughout the intervention through reports from participants or their guardians and through contacts with the clinical-research team. Participants and guardians will be instructed to report any health problems occurring during the study, irrespective of its presumed relationship with the intervention. All reported health problems and adverse events will also be recorded as incidents. In addition, each time participants open the Diactive-1 app after a completed session, they will be asked whether they experienced any hypoglycemic episode in the hours following the previous Diactive-1 session. These app-recorded post-session hypoglycemic events will be used to complement adverse-event monitoring and will be reviewed by the clinical-research team when appropriate. All adverse events will be recorded in the case report form.

Exercise sessions may be temporarily interrupted or permanently discontinued in the event of a serious adverse event, recurrent severe hypoglycemia, persistent hyperglycemia with ketosis, acute illness, injury, or any new medical condition contraindicating exercise participation. Discontinuation of the intervention for these motives will not automatically imply withdrawal from study follow-up, unless requested by the participant or guardian.

Serious adverse events will be reported to the relevant ethics committee and competent institutional bodies according to local regulations and hospital-specific procedures.

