**Figure 2 f2:**
[figure not shown]
Programmed progression of training volume and recovery intervals for the classic, circuit, and Tabata resistance-training modalities in Diactive-1: **(A)** classic and circuit training; **(B)** Tabata training.

Diactive-1 (v.2.0) requires participants to enter glucose values before and after each training session. These values are used to provide educational messages based on CGM readings (18). In this updated version, additional messages are provided for participants using the Medtronic MiniMed 780G automated insulin delivery system (19), reflecting its frequent use in the participating Spanish clinical settings. These messages are intended to support type 1 diabetes self-management and the safe completion of the corresponding resistance-training session. In general, messages for hyperglycemia focus on insulin-dose adjustment, while messages for hypoglycemia focus on rapid-acting carbohydrate intake according to the participant’s body mass. Specifically, training is not permitted when glucose is <70 mg/dL (<3.9 mmol/L) or when glucose is >270 mg/dL (>15.0 mmol/L) with ketone levels >1.5 mmol/L. Conversely, when interstitial glucose is >270 mg/dL (>15.0 mmol/L), trending upward, and ketone levels are <1.5 mmol/L, the app provides short continuous aerobic exercise sessions to support insulin bolus–mediated correction of hyperglycemia before reassessing eligibility for resistance training. As a further update, Diactive-1 (v.2.0) includes “Did you know?” loading-screen messages summarizing findings from scientific studies linking muscular strength with health benefits, aiming to make research evidence accessible to youth with type 1 diabetes.

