#### Intervention participation measurement

2.8.4

Intervention participation will be assessed through app access data, and completed sessions will be defined as sessions that are started and fully completed; the type of session, the number of exercises performed, and the number of sets and repetitions will be recorded. At the end of each session, participants will report their perceived exertion using the modified Borg scale from 0 (“not intense”) to 10 (“extremely intense”) (34). Thus, participation data will capture both session completion and the perceived intensity of each completed session for all participants. Every Thursday, participants will receive a notification indicating the number of sessions completed that week, allowing three remaining days within the Monday-to-Sunday period to meet ADA recommendations (20).

These measures will be supplemented by mean and maximum heart rate recorded using the Polar Verity Sense monitor (Polar Electro, Kempele, Finland) in participants recruited from four randomly selected hospitals. Because of resource constraints, heart-rate monitoring will be limited to this subsample and will provide complementary objective information rather than define intervention exposure. Exercise execution quality will not be formally assessed; however, standardized tutorials, 3D exercise demonstrations, and narrated technique cues will be provided to support correct and safe execution.

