### Secondary outcomes

2.10

Secondary outcomes assessed in Diactive-1 are summarized in **Table 1**. Secondary outcomes are organized hierarchically in: key secondary outcomes (i.e., glycemic-stability parameters and insulin requirements); descriptive or contextual outcomes (i.e., sociodemographic information, diabetes-related clinical characteristics, anthropometric parameters, pubertal maturation, intervention engagement, and barriers to physical activity); and exploratory or hypothesis-generating outcomes, including cardiovascular biomarkers and lipid profile; lifestyle-related outcomes (i.e., 24-hour movement behaviors and adherence to the Mediterranean diet); physical-domain outcomes (i.e., self-reported physical fitness and physical literacy); mental and psychosocial outcomes (i.e., psychological assessments, health-related quality of life, and screening for eating disorders); and implementation-related outcomes intended to explore usability, acute glycemic responses, and potential dose-response relationships (i.e., app usability and data recorded by the Diactive-1 app).

**Table 1 T1:** Summary of the variables examined in the randomized clinical trial.

Primary outcome	Measurement	Tool
Handgrip strength	Directly: Objectively	- Takei III Smedley Type 297 digital dynamometer. - Age- and sex-standardized z-score calculated using FitBack^©^ reference values.
Secondary Outcome	Measurement	Tool
Glycemic stability	Indirectly: - Objectively	- CGM downloads. (without brand distinction)
Insulin requirements	Indirectly: - Objectively - Self-reported	- Insulin pump downloads. - Smart-pen logs. - Insulin records from participants using CGM. (without brand distinction)
Cardiovascular biomarkers and lipid profile	Directly: - Objectively	- Laboratory testing at each hospital’s central laboratory. (standardized protocols)
Anthropometric parameters	Directly: - Objectively	- Height: SECA 213 stadiometer. - Weight: SECA electronic scale.
Maturity status	Indirectly: - Objectively	- Peak height velocity: Moore’s equation. - Tanner scale.
Self-reported fitness	Subjectively: - Self-reported	- International Fitness Scale (IFIS)
Physical literacy	Subjectively: - Self-reported	- Spanish Perceived Physical Literacy Instrument (S-PPLI)

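### The app's hypoglycemia question is tied to fully completed sessions and to the hours afterwards, so app-recorded exercise-related hypoglycemia is likely understated

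*Protocol article*

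**What the plan says.** Section 2.8.4 sets the unit of participation: "completed sessions will be defined as sessions that are started and fully completed".

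Section 2.12 makes that unit the trigger for the hypoglycemia item: "each time participants open the Diactive-1 app after a completed session, they will be asked whether they experienced any hypoglycemic episode in the hours following" that session. The same section says these answers complement adverse-event monitoring. That monitoring also runs through scheduled visits, reports from participants and guardians, and contacts with the clinical-research team.

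Section 2.10.17 opens its list of app data with "For each completed session, recorded variables will include the session number, date and time of completion". A separate sentence follows: "The app will also record diabetes management variables, including pre- and post-session glucose values". That sentence includes the hypoglycemia item as "hypoglycemic events reported since the previous session". Section 2.8.3 states the glucose rule without a completion condition: the app "requires participants to enter glucose values before and after each training session".

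Section 2.10 places the app data among "implementation-related outcomes intended to explore usability, acute glycemic responses, and potential dose-response relationships", within the exploratory tier. Section 2.14 lists app-recorded safety information among the items reviewed in trial monitoring.

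**The concern.** Whether a session is finished can depend on whether the participant went low during it. A question asked only after finished sessions therefore selects on the event it is meant to count. A participant who feels low at the third of five exercises, stops and treats it has not completed the session. Under Section 2.12 that session raises no question. Even after a finished session, the question covers the hours that follow and not the session itself.

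At stake is the trial's own description of how often exercise under the app is accompanied by hypoglycemia. The Introduction names fear of hypoglycemia as a main barrier to exercise, and it cites the absence of reported hypoglycemic events in the previous trial as a favorable result. A low app-recorded rate here could be read the same way, even if part of it reflects when the question is asked.

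**Working it through.** The protocol states no event rate for this item, so there is no figure to reproduce. The check compares the sections and then illustrates direction and size under stated assumptions.

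**1. What triggers a record**

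| Item | Section | Condition as written |
|---|---|---|
| Completed session | 2.8.4 | started and fully finished |
| Hypoglycemia question | 2.12 | app opened after a completed session; hours afterwards |
| Hypoglycemia variable | 2.10.17 | since the previous session; completion not repeated |
| Session variables | 2.10.17 | each completed session |
| Pre- and post-session glucose | 2.10.17 | separate sentence; completion not repeated |
| Glucose entry | 2.8.3 | each training session |
| App parameters generally | Table 2, note d | continuously during app use |

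Sections 2.8.4 and 2.12 together settle the prompt: a stopped session does not trigger it, and in-session lows are outside its wording. They do not settle post-session glucose, where Sections 2.8.3 and 2.10.17 can be read either way. No section describes a record or a reason for a session stopped early.

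**2. Recall window**

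If the window runs since the previous session, its average length depends on training frequency:
- 2 sessions a week: 7 × 24 / 2 = 84 h
- 3 sessions a week: 7 × 24 / 3 = 56 h

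Taking 12 h for the hours following a session (an assumption; the protocol gives no number), the ratios are 84/12 = 7.0 and 56/12 = 4.7. The two wordings therefore describe clearly different exposure times. Under the longer one, exposure per prompt changes with training frequency, which Section 2.15 plans to use as a dose-response exposure.

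**3. Effect of restricting to completed sessions**

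Let h be the true risk of hypoglycemia in a session, s the share of hypoglycemic sessions stopped early, and q the share of other sessions stopped early. Among completed sessions the risk is

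observed = h(1−s) / [h(1−s) + (1−h)(1−q)].

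This is below h exactly when s > q. All three inputs are assumptions. With q = 5%:

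| h | s | Observed |
|---|---|---|
| 10% | 0% | 10.5% |
| 10% | 25% | 8.1% |
| 10% | 50% | 5.5% |
| 10% | 75% | 2.8% |
| 5% | 50% | 2.7% |
| 20% | 50% | 11.6% |

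For h = 10% and s = 50%: 0.05 / (0.05 + 0.90 × 0.95) = 0.05 / 0.905 = 5.5%.

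The formula supposes that lows within completed sessions are captured. The Section 2.12 wording does not ask about those either, so for the prompt alone the loss of in-session lows goes further.

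**4. What CGM can recover**

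Section 2.10.1 collects CGM for 14 days before and 7 days after each visit. Section 2.11 activates the app only after baseline collection is verified, so neither baseline window contains training. The 7 days after the Week 12 visit fall after the 12 weeks. The overlap with the intervention is therefore about 14 of 12 × 7 = 84 days (14/84 = 17%), leaving about 70 days uncovered.

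**The case against.** The strongest reply has four parts.

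First, a reader might infer that post-session glucose is stored only for finished sessions. The text does not establish that: Section 2.8.3 requires entry around each training session, and the glucose sentence in Section 2.10.17 does not repeat the completion condition. This stands, so the glucose point is an ambiguity to reconcile and not a demonstrated loss. Likewise, if the window runs since the previous session, a low in an aborted session could be reported at a later prompt. That is correct, but it means the two sections disagree on whether such a low is captured.

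Second, a reader might infer that these events vanish from safety monitoring altogether. They do not. Section 2.12 provides active monitoring at visits, asks families to report any health problem whatever its presumed cause, and calls the app answers complementary. This also stands. Those channels supply no session glucose values, however, and could miss mild, self-treated lows.

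Third, the consequence is limited. The acute-glycemic outcome is exploratory and available only in the app arm during the trial. Between-group hypoglycemia comes from CGM in both arms, independent of session completion, and Section 2.15 does not name the prompted count as a dose-response outcome. All of this is right and limits the weight of the point.

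Fourth, the handling of aborted sessions may be app detail that an article leaves to the full protocol, and the session-sequence figure is not shown. That would answer a complaint about missing detail. It does not answer a trigger that is stated and selects on the event, or two stated windows that differ.

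**Conclusion.** The point holds for the app's hypoglycemia prompt. It is conditioned on full completion, asks only about the period afterwards, and is described with two different windows. For post-session glucose the documents are unclear.

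The app-recorded rate of exercise-related hypoglycemia is likely understated, provided that hypoglycemic sessions are stopped more often than others (s > q). If none were stopped early, the restriction would not lower the rate: 10.5% against a true 10% in the illustration. No size can be taken from the documents, and any count of lost events would only restate assumed rates.

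The effect is confined to an exploratory, single-arm outcome and to complementary safety information. The primary handgrip analysis and the key secondary glycemic and insulin outcomes are not touched. The change is still worth making early, because session data not captured during follow-up cannot be reliably recovered.

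**What to change.** - Trigger the post-session glucose entry and the hypoglycemia item for every session started, including those stopped early, and record a reason for stopping.
- Ask about lows during the session as well as after it.
- Use one fixed recall window, worded identically in Sections 2.10.17 and 2.12.
- Reconcile Sections 2.8.3, 2.8.4, 2.10.17 and 2.12 on what is recorded for completed and for stopped sessions.
- Report app-recorded hypoglycemia per session started, with the number stopped early shown beside it.

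A timed notification, so that the question does not depend on the participant reopening the app, is optional.

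The cost is a small app update, a few sentences in the protocol, and one short extra prompt per aborted session. The change concerns data capture only and leaves clinical management as it is.

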#### Glycemic stability

2.10.1

Glycemic parameters, including CGM wear time, mean glucose, glucose management indicator (GMI), time well above range (%TwAR; >250 mg/dL [>13.9 mmol/L]), time above range (%TAR; 180–250 mg/dL [10.1–13.9 mmol/L]), time in range (%TIR; 70–180 mg/dL [3.9–10.0 mmol/L]), time below range (%TBR; 54–70 mg/dL [3.0–3.8 mmol/L]), time well below range (%TwBR; <54 mg/dL [<3.0 mmol/L]), glycemic coefficient of variation (CV), hypoglycemic events (i.e., values <70 mg/dL [<3.9 mmol/L] lasting ≥15 min), and nocturnal hypoglycemic events (i.e., hypoglycemic events between 10:00 p.m. and 08:00 a.m.), will be obtained from CGM software regardless of the brand used.

Data will be collected during continuous 14-day monitoring periods before the baseline and 12-week medical visits (36). For descriptive and exploratory purposes, CGM data will also be collected during the 7 days after each visit, corresponding to the period in which carbohydrate intake and insulin-correction doses are prospectively recorded (37).

Glycemic targets will be evaluated according to ADA guidelines (38): HbA1c <7%, CV ≤36%, TwAR <5%, TAR <25%, TIR >70%, TBR <4%, and TwBR <1%. The glycemic risk index (GRI) score will be calculated as follows: (3.0 × TwBR) + (2.4 × TBR) + (1.6 × TwAR) + (0.8 × TAR) (39).

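### Post-session hypoglycemia is asked about in the app arm only and joins adverse-event monitoring with no stated source separation, so by-arm counts that pool it would tend to be inflated in that arm

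*Protocol article*

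**What the plan says.** Section 2.12 (Adverse event reporting and harms) sets up two routes by which hypoglycemia can come to notice.

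The first is common to both arms: "adverse events will be actively monitored at the scheduled study visits and throughout the intervention through reports from participants or their guardians", together with contacts with the clinical-research team. It adds: "Participants and guardians will be instructed to report any health problems occurring during the study, irrespective of its presumed relationship with the intervention". Neither sentence is limited to one arm.

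The second exists only for app users: "each time participants open the Diactive-1 app after a completed session, they will be asked whether they experienced any hypoglycemic episode" in the hours after that session. The use of the answers is stated: "These app-recorded post-session hypoglycemic events will be used to complement adverse-event monitoring", with review by the clinical-research team when appropriate. The same paragraph closes with: "All adverse events will be recorded in the case report form".

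Usual-care participants cannot receive the prompt during follow-up. Note b to Table 2 says that they "will be offered Diactive-1 access after post-T1 7-day data collection", and section 2.8.2 agrees.

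Section 2.10.1 provides a device-based measure in both arms, including hypoglycemic events, nocturnal events and time below range: "Data will be collected during continuous 14-day monitoring periods before the baseline and 12-week medical visits". Section 2.10 ranks the glycemic parameters as key secondary outcomes and the app-recorded data as exploratory, implementation-related outcomes.

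**The concern.** When one arm is asked a direct question repeatedly and the other is not, the first arm will usually record more events, whatever the true rates. Here the question concerns hypoglycemia, which the Introduction names as a primary barrier to exercise in these patients and which is the obvious harm to examine for this intervention. The article also summarizes the earlier single-center trial as having had no reported hypoglycemic events, so reported events are already part of how the program's safety is described.

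If prompted answers and commonly ascertained events reach the same form unmarked, a harms table by arm can show an excess in the app arm that comes from the questioning. A reader who knows this may then discount a true excess as an artefact. Either way the table would be hard to interpret. How harms are tabulated can be left to an analysis plan, but whether the source of each event is recorded is settled at data collection.

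**Working it through.** The plan states no figure on this point, so there is none to reproduce. The check sets the ascertainment routes side by side and then illustrates the possible size.

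**Routes during the 12 weeks**

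| Route | App arm | Usual care | Where stated |
|---|---|---|---|
| Scheduled study visits | yes | yes | 2.12; Table 2 shows assessments at baseline and week 12 only |
| Participant or guardian reports, team contacts | yes | yes | 2.12 |
| App prompt after a completed session | yes | no | 2.12; 2.8.2; Table 2 note b |
| CGM-defined events, 14 days before each visit | yes | yes | 2.10.1; CGM use required by 2.3 |

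Only the third row differs between arms.

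**Number of extra prompts.** Two sessions a week is the per-protocol threshold in section 2.15. Three matches the muscle-strengthening frequency that the Introduction cites from the guideline. One prompt per completed session is the maximum, because the question appears only when the app is next opened.

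- Per app user: 2 × 12 = 24; 3 × 12 = 36.
- All 79 randomized: 79 × 24 = 1,896; 79 × 36 = 2,844.
- The 67 per group expected to be evaluable (section 2.4): 67 × 24 = 1,608; 67 × 36 = 2,412.
- Usual care: 0.

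The totals are ceilings, since they assume everyone counted trains at that rate throughout.

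**How unequal capture would appear in a pooled count.** With equal true event rates,

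apparent rate ratio = (share of episodes captured in app arm) ÷ (share captured in usual care).

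The documents give no capture shares, so these are assumptions:

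- 0.8 against 0.4: 0.8 / 0.4 = 2.0
- 0.8 against 0.6: 0.8 / 0.6 = 1.33
- 0.6 against 0.6: 1.0, no distortion

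For the proportion of participants with at least one recorded event, treat the shares as the chance that an affected participant is recorded and assume a true risk of 30% to 50% in both arms. The spurious risk difference is risk × (difference in shares):

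- 0.8 against 0.4: 0.30 × 0.4 = 0.12, up to 0.50 × 0.4 = 0.20
- 0.8 against 0.6: 0.30 × 0.2 = 0.06, up to 0.50 × 0.2 = 0.10

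All of this applies only if prompted events are pooled with the rest.

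**What the CGM outcome covers.** The key-secondary on-treatment window is 14 of 12 × 7 = 84 days: 14 / 84 = 16.7%. The 7-day post-visit CGM data fall before app activation (after the baseline visit) or after the week-12 visit, and are labelled descriptive and exploratory. For the remaining 84 − 14 = 70 days, the adverse-event system is the only between-arm source on hypoglycemia that the article specifies.

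**The case against.** The strongest reply is that the comparison at risk is not in the document. Section 2.15 names no adverse-event comparison between arms; its risk differences and number needed to harm concern categorical outcomes, and adverse events are not listed among the outcomes. Tabulation by source may sit in an analysis plan that is not shown. This stands, and it makes the bias conditional.

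Second, section 2.14 lists app-recorded safety information apart from adverse event records, and section 2.12 does not say that every positive answer becomes an adverse event. This also stands: pooling is a possibility, not a stated step. But listing two items for monitoring does not say that they stay apart in reporting, and the common form carries no stated source marker.

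Third, usual care is not left to spontaneous reporting. It has active inquiry at visits and the same instruction to report. A reader might infer that solicited reports in one arm face only volunteered reports in the other; section 2.12 does not support that.

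Fourth, a symmetric hypoglycemia measure already exists. CGM events use one definition and the same windows in both arms, and the prompt cannot affect them. A reader might infer that the trial's hypoglycemia comparison as a whole is biased against the app; it is not. The limit is coverage, not asymmetry.

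Finally, a question about the hours after a session cannot be put to people who have no sessions. Asking it is reasonable safety surveillance. The issue is only how the answers are recorded and counted.

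**Conclusion.** The point holds in a conditional form. The protocol article fixes an ascertainment route that only the app arm has, gives its answers a role in adverse-event monitoring, and states no separation by source on the common form. By-arm adverse-event counts that pool the two kinds of report would tend to be inflated in the app arm even if the true rates were equal.

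The size cannot be determined from the document. The ceiling of about 24–36 extra prompts per app user rests on 2–3 completed sessions a week for the full 12 weeks. The apparent rate ratios of 1.33 to 2.0 rest on assumed capture shares, and equal capture would give 1.0. Nothing in the text supports the claim that a prespecified harms comparison is already biased, or that every positive answer would have no counterpart in usual care. The CGM-defined outcome is unaffected, but its 14-day window cannot stand in for adverse-event capture over the whole period. The change is worth making because it is nearly free and because an unflagged form is hard to separate afterwards.

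**What to change.** 1. Add a source field to the adverse-event form: scheduled visit, participant or guardian report, team contact, or app prompt.
2. State in section 2.12 that app-prompted hypoglycemia is reported separately and descriptively, for the intervention arm only.
3. State in section 2.15 that between-arm adverse-event counts use only the sources common to both arms: scheduled visits, participant or guardian reports, and team contacts.
4. Name the CGM-defined hypoglycemic events already planned in section 2.10.1, over identical windows, as the between-arm hypoglycemia comparison.

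Review of app reports for safety stays as planned.

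The cost is a few sentences and one form field, with no new assessment of participants. Section 2.4 allows enrollment through September 30, 2026, so the earlier the flag is added, the fewer records will lack it. For events entered before then, the session-level app data described in section 2.10.17 may help identify the source, though not always cleanly.
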